### Randomization

All registered patients will be randomly assigned to the intervention group or the control group with a ratio of 1:1. Randomizing the sequence column order will be performed according to the predefined table generated by a computer software program. The random sequence will be hidden in a closed opaque envelope. Before initiating the study, the envelopes will be prepared by research assistants who are not directly involved in the research project. After recording baseline measures, participants will be randomly allocated to either the RIC or control group by the treating physicians who will open the sealed opaque envelopes.

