**Figure 2 F2:**
[figure not shown]
Procedure timeline **(A)** RIC group; **(B)** Control group (Sham-RIC).

Epworth Sleepiness Scale, the Pittsburgh Sleep Quality Index (PSQI), and Parkinson's Disease Sleep Scale-2 (PDSS-2) are to be used to assess the common sleep problems of Parkinson's patients (44, 45). The Parkinson's Disease Questionnaire 39 (PDQ39) is to be used to assess the quality of life of Parkinson's patients (46), which is administered by trained investigators blinded to the treatment assignment. The assessments are performed on the day of enrollment for baselines and 7, 14, 28, and 90 days after the enrollment.

Patients will continue their home medications to manage chronic conditions, including Parkinson's disease, according to the recommendations of the International Parkinson and Movement Disorder Society (15, 47).

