### Outcomes

#### Outcomes for feasibility and efficacy

The primary outcomes of this study are to assess the feasibility and efficacy of RIC from changes of ESS, PSQI, PDSS-2, and PDQ39 scores from the baselines to post-treatment on days 7, 14, 28, or 90. This study will determine (1) whether ESS, PSQI, PDSS-2, and PDQ39 can be performed in the patients and (2) the differences between ESS, PSQI, PDSS-2, and PDQ39 in patients with or without RIC. Certified therapists and assistants will collect data from the subjects and the obtained information will be used for statistical analysis.

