### Sample size estimation

This is a phase 1 test measuring the safety and feasibility of RIC. Because there has not been a clinical study on RIC for Parkinson's patients, there is no data for reference at this point. Hertzog (48) suggests that 10–20 patients in each group are enough to evaluate the feasibility of a pilot study. Dobkin et al. explain that most phase 1 clinical rehabilitation pilot studies start with samples of 6–12 participants (49). Based on studies addressing the safety and feasibility of RIC, this project targets 20 patients in each group. The results of this study will be used not only to determine the safety and feasibility of RIC but also to estimate the sample size and calculate the power required for the phase 2 test in the future.

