### Statistical analysis

Data are obtained from all patients who complete the study protocols and follow-ups. They will be analyzed by per-protocol (PP) analysis. Statistical analysis will be performed using SPSS version 19 (SPSS Inc., Chicago, IL, USA). *P* < 0.05 will be considered statistically significant. Demographics and clinical characteristics will be analyzed for descriptive statistics. Continuous and categorical data will be presented as mean values, standard deviations, number values, and percentages. Continuous variables consistent with the normal distribution will be compared by the independent samples *t*-test or ANOVA or rank-sum test. Categorical variables will be compared by chi-square testing.

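### Continuous outcomes get unadjusted two-group tests with no usable rule for choosing between them, and baseline enters at most by subtraction although every scale is measured at enrolment

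*Protocol article*

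**What the plan says.** All references are to the protocol article.

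- **Tests.** Statistical analysis: "Continuous variables consistent with the normal distribution will be compared by the independent samples" t-test, or by "ANOVA or rank-sum test". The threshold is that P below "0.05 will be considered statistically significant". The section names no covariate, no repeated-measures model, and no test for continuous variables that fail normality.
- **Data collected.** Interventions, in the text after Figure 2: "The assessments are performed on the day of enrollment for baselines and 7, 14, 28, and 90 days after the enrollment".
- **Outcome scale.** Outcomes for feasibility and efficacy describes the primary outcomes in two ways. One is "changes of ESS, PSQI, PDSS-2, and PDQ39 scores from the baselines to post-treatment on days 7, 14, 28, or 90". The other is "the differences between ESS, PSQI, PDSS-2, and PDQ39 in patients with or without RIC", which does not mention change.
- **Size and allocation.** Sample size estimation: "this project targets 20 patients in each group". Randomization: allocation "with a ratio of 1:1", with no stratification described.

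**The concern.** There are two linked problems.

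**The sentence does not work as a rule.** The rank-sum test is listed for normally distributed variables, where it is not the natural choice, and non-normal variables are left without a test. With two arms, a one-way ANOVA is the t-test, so the real choice is t-test or rank-sum. Nothing says who makes that choice, when, or on what criterion. The Outcomes section also leaves open whether the score at the visit or its change from baseline is compared.

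**The baseline score is not used as well as it could be.** On the change-score reading it is subtracted; on the post-score reading it is not used at all. Either way, the estimate is less precise than the collected data allow and keeps part of any chance difference between the arms at entry. This matters because Sample size estimation says the results will be used to size and power the phase 2 trial. A noisy or shifted estimate would carry into that calculation.

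**Working it through.** **Inputs.** From the article: 20 per arm, 1:1, alpha 0.05 (two-sided assumed), entry at ESS 10 or above, and EDS in 16–50% of patients (Introduction). The article gives no SD, effect size, power or correlation, so it has no figure of its own to reproduce. Assumed: baseline-to-follow-up correlation r from 0.3 to 0.7, and unit SD.

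**1. Equal variances at baseline and follow-up (at most PSQI, PDSS-2, PDQ39).** Variance factors are 1 for the post score, 2(1−r) for the change score and 1−r² for ANCOVA. Hence ANCOVA/change = (1+r)/2 and ANCOVA/post = 1−r².

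| r | ANCOVA/change | ANCOVA/post | Change-score n per arm to match ANCOVA at 20 | Post-score n per arm |
|---|---|---|---|---|
| 0.3 | 0.65 | 0.91 | 30.8 | 22.0 |
| 0.5 | 0.75 | 0.75 | 26.7 | 26.7 |
| 0.7 | 0.85 | 0.51 | 23.5 | 39.2 |

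The difference detectable with 80% power (normal approximation) is (1.960 + 0.842) × √(2/20) × √variance. At r = 0.5 this is 0.89 SD for either unadjusted analysis and 0.77 SD for ANCOVA.

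**2. ESS, truncated at entry.** Assume a bivariate normal model with equal variances before selection, and let the cut-off select the top 16% to 50% of patients. Baseline variance falls to v = 0.20 (top 16%) or 0.36 (top 50%) of its unselected value. The residual variance 1−r² is unchanged, and the change-score variance becomes (1−r²) + (1−r)²v. Hence ANCOVA/change = (1+r) / [(1+r) + (1−r)v].

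| unselected r | v = 0.36 | v = 0.20 |
|---|---|---|
| 0.3 | 0.84 | 0.90 |
| 0.5 | 0.89 | 0.94 |
| 0.7 | 0.94 | 0.97 |

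At r = 0.5, 20/0.892 = 22.4 and 20/0.938 = 21.3, so the gain is worth about 1 to 2 patients per arm.

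Against a post-score t-test the ratio is 1−r², with r taken within the enrolled patients. An unselected 0.5 becomes r√v / √(1−r²+r²v) = 0.33 (v = 0.36) or 0.25 (v = 0.20), which gives 0.89 or 0.94.

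These ratios leave out the cost of estimating the slope. With a normal baseline that factor averages 1 + 1/(2×20−4) = 1 + 1/36, or about 1.03, so the ESS gain is slightly smaller still.

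**3. Chance imbalance (equal variances).** A baseline difference D shifts the post-score estimate by +rD and the change-score estimate by −(1−r)D. At r = 0.5 and D = 0.5 SD, that is 0.25 SD in opposite directions. The standard error of D is √(2/20) = 0.32 SD, so |D| exceeds 0.3 SD in about 34% of such trials and 0.5 SD in about 11%.

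**4. Free choice of test.** In a null simulation of 40,000 trials with 20 per arm, taking the smaller p-value of t-test and rank-sum gave a type I error of 0.061 for normal data and 0.064 for skewed or heavy-tailed data. Allowing post score or change score as well gave 0.110 at r = 0.5 and 0.111 at r = 0.7. One-way ANOVA and the t-test gave the same p-value on one data set (0.184).

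**The case against.** Four points on the other side deserve weight.

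- **Baseline is not simply ignored.** A reader of the Statistical analysis section alone might infer that it is. The Outcomes section names change from baseline, so that reading is not supported. What remains is that subtraction is less efficient than adjustment, and that the same section also speaks of differences between the scores.
- **The gain for ESS is small.** It is tempting to apply the equal-variance figure (27 rather than 20 per arm at r = 0.5) to the scale that defines the population. The entry criterion of ESS 10 or above makes this unsafe: truncation cuts baseline variance and shrinks the gain to a few patients at most. This stands.
- **The choice of test matters little by itself.** A reader might infer serious error inflation. Between t-test and rank-sum it is about one percentage point. The larger figure needs the outcome scale to be open too, and the rank-sum test is plausibly a misplaced fallback for non-normal data.
- **This is a condensed report of a pilot.** Both t-test readings are unbiased under randomisation, the trial has no power target, and the unspecified ANOVA could be a repeated-measures form. Nor is a loss from comparing visits separately shown: with completers only and an unstructured covariance, a repeated-measures model gives the same contrast at a visit as simple ANCOVA. These points limit the severity. They do not rescue a sentence that states its rule wrongly, in an article that makes efficacy a primary outcome and sets a significance threshold.

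**Conclusion.** The point holds in limited form. The test sentence is wrong as written, because it gives three tests under normality, no rule for choosing and nothing for non-normal data. The analysis also passes up a precision gain that needs no new data.

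The gain over a change-score t-test is a variance ratio of 0.65 to 0.85 for PSQI, PDSS-2 and PDQ39 at most, and nearer 0.84 to 0.97 for ESS. These rest on assumed r of 0.3 to 0.7, on equal variances for the first range, and on a normal selection model for ESS. The possible type I error for one comparison is about 0.06 from the choice of test alone and about 0.11 if the outcome scale is open too.

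In a pilot with no powered hypothesis, the consequence lies in the precision of the estimates and in the phase 2 sample size built on them. The documents do not support reading this as a threat to a confirmatory conclusion. The change should be made, but the trial does not fail without it.

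**What to change.** Replace the sentence on continuous variables with one baseline-adjusted analysis per scale and visit. Either of these serves:

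- ANCOVA of the score at each visit on treatment and the baseline score of the same scale. Post score and change score then give the same treatment estimate, so the ambiguity in the Outcomes section no longer affects the result.
- An equivalent repeated-measures model over days 7, 14, 28 and 90, with treatment, visit, treatment-by-visit, baseline and baseline-by-visit.

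Report the treatment difference with its 95% CI at each of the four visits. Do not single out day 28 as part of this change, because the article does not set it as the primary time point. Keep a rank-based analysis only as a sensitivity check stated in advance, not as an alternative chosen after a look at the data.

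The cost is analysis wording only, with no new patient, visit or measurement. ANCOVA spends one degree of freedom on baseline per analysis; the repeated-measures form spends four baseline parameters per scale (baseline plus its interaction over four visits).

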**Results:**

The primary goal of this study is to assess the feasibility of the treatments in patients with Parkinson's disease by measuring serious RIC-related adverse events and any reduced incidence of adverse events during the trial and to study potential efficacy, improvement of patients' excessive daytime sleepiness, quality of life-based on ESS, PSQI, PDSS-2, and PDQ39 scores. The secondary goal is to confirm the safety of the treatments.

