#### Outcomes for safety

The secondary outcome of this study is to assess the safety of RIC. Any serious RIC-related adverse events are the following: (1) inability to tolerate RIC or sham-RIC procedures leading to the suspension of the study; (2) signs of tissue or neurovascular injury caused by RIC and sham RIC operations (e.g., palpation of distal radial artery pulsation, visual inspection of local edema, erythema and skin damage, or palpation of tenderness). All adverse events will be independently determined by trained individuals of the research group who are blinded by random grouping.

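### The abstract aims to confirm safety, but a significance test on 20 patients per arm with no safety margin can only estimate it: 0/20 events still leaves rates up to 16.8% open

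*Protocol article*

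**What the plan says.** The Results paragraph of the abstract sets a confirmatory safety goal: "The secondary goal is to confirm the safety of the treatments". The section on outcomes for safety is milder: "The secondary outcome of this study is to assess the safety of RIC". That section lists the events of interest: intolerance of the procedure that leads to suspension, and signs of tissue or neurovascular injury. For each patient these are yes/no outcomes.

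The Statistical analysis section gives one comparison for such data: "Categorical variables will be compared by chi-square testing". The threshold in the same section is a P-value under 0.05: "0.05 will be considered statistically significant". Categorical data will also be shown as numbers and percentages. On the analysis set it says: "They will be analyzed by per-protocol (PP) analysis", and it limits the data to patients who complete the protocol and follow-up.

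The size is set by pilot precedent: "this project targets 20 patients in each group". The same section says that "there is no data for reference at this point". No event rate, margin or power for safety is given.

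**The concern.** To confirm that a treatment is safe, a trial must exclude an event rate, or an excess over control, that would be unacceptable. That takes a stated limit and an interval lying below it. The protocol states no limit. Its one inferential tool tests for a difference, and with 20 per arm that test fails to reject over a wide range of true harm. In the most favourable case, with no events in either arm, the statistic cannot be computed.

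The sample size section says that the results will inform phase 2. A report that safety was confirmed, when the data remain compatible with a serious event rate near 17%, would give that decision more reassurance than it has.

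**Working it through.** **Inputs.** 20 patients per arm (Sample size estimation); 1:1 allocation (Randomization); chi-square at P < 0.05 (Statistical analysis). Sidedness is not stated; a chi-square test on a 2×2 table is two-sided. The documents give no event rates, so every rate below is an assumption. The plan contains no safety calculation to reproduce.

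**1. What a clean arm excludes.** With 0 events in n patients, the exact (Clopper-Pearson) two-sided 95% upper limit is 1 − 0.025^(1/n), and the one-sided 95% limit is 1 − 0.05^(1/n).

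| Result | Two-sided upper limit | One-sided upper limit |
|---|---|---|
| 0/20 | 16.8% | 13.9% |
| 0/18 | 18.5% | 15.3% |
| 0/16 | 20.6% | 17.1% |
| 0/15 | 21.8% | 18.1% |

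The rows below 20 show the effect of restricting the analysis to completers. If the true rate were 10%, an arm of 20 would still show no event with probability 0.9^20 = 12%.

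**2. What the test does with sparse tables (20 per arm).**

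| Events | Uncorrected chi-square P | Yates P | Fisher P |
|---|---|---|---|
| 0 vs 0 | undefined | undefined | 1 (uninformative) |
| 0 vs 3 | 0.072 | 0.230 | 0.231 |
| 0 vs 4 | 0.035 | 0.114 | 0.106 |
| 0 vs 5 | 0.017 | 0.056 | 0.047 |

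For 0 vs 3, chi-square = 40 × (3×20 − 0×17)² / (20 × 20 × 3 × 37) = 144,000 / 44,400 = 3.24, so P = 0.072. An observed 15% against 0% is therefore not significant, even with the most liberal of the three tests.

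**3. Power, by exact enumeration of all tables at 20 per arm.**

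| Assumed true rates | Uncorrected chi-square | Fisher |
|---|---|---|
| 0% vs 10% | 13% | 4% |
| 5% vs 15% | 15% | 7% |
| 5% vs 20% | 29% | 17% |
| 5% vs 30% | 59% | 45% |
| 5% vs 40% | 82% | 72% |

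Among these pairs, power passes 80% only at 5% against 40%. Detecting 5% against 15% with 80% power would need about 141 per arm.

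**4. Type I error.** With equal rates in both arms, the enumerated size of the uncorrected chi-square is 0.012 at 5%, 0.039 at 10%, 0.050 at 20% and 0.053 at 30%. The test is conservative at low rates and close to nominal above that.

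**5. The analysis set.** A patient who stops because the procedure cannot be tolerated has a listed serious event, yet may not complete the protocol. A completers-only analysis can then lose both the event and the patient, so an observed 0/n need not mean that no treated patient had an event. The limits in step 1 hold for the treated population only if all treated patients are counted.

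**The case against.** The strongest reply is that the document, read as a whole, does not claim a confirmatory safety design. The verb confirm is applied to safety only in the abstract. The body uses assess, evaluate or determine, calls the trial a phase 1 test and leaves power to a later study. Twenty per group is reasonable for a pilot. This stands: the size is not the error.

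A reader might go further and infer that the sponsor will take P ≥ 0.05 as proof of safety. The protocol does not say so. The Statistical analysis section is a general list of tests, does not name adverse events and sets no safety decision rule.

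A reader might also infer that chi-square is invalid here because expected event counts fall below 5 whenever fewer than 10 of the 40 patients have an event. The counts are indeed sparse and P depends on the version used, but step 4 shows no material inflation of the type I error. Nor is Fisher's exact test a clear improvement: for 5% against 20% it lowers power from 29% to 17%, which is the wrong direction when the worry is overlooked harm.

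Finally, numbers and percentages are already planned, and an article may leave interval methods to a fuller document. That is fair as to detail. It does not remove the mismatch between a stated goal and the stated means of reaching it.

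**Conclusion.** The concern holds in a limited form. A goal of confirming safety is not achievable with 20 patients per arm, no acceptable rate or margin, and a test of difference as the only stated comparison. The best possible result in one arm, 0/20, leaves event rates up to 16.8% open (two-sided exact 95%; 13.9% one-sided), and more if completers alone are counted. The power figures rest on assumed rates and vary widely with them, from 13% to 82% over the pairs shown. The 16.8% needs no assumed rate, only that all 20 patients are analysed. The conclusion concerns the wording of the goal and the way safety is summarised. It does not concern the sample size or the validity of the chi-square test, and it does not attribute to the sponsor a rule that non-significance means safe.

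**What to change.** - In the abstract, replace the aim of confirming safety with estimating the adverse event rate, in line with the milder wording of the safety outcomes section.
- Report each safety outcome as count and proportion per arm with an exact (Clopper-Pearson) 95% interval, and the risk difference with a score-based 95% interval. State that 0/20 would exclude only rates above about 17% (two-sided).
- Do this in all patients who received at least one RIC or sham session, not in completers only.
- Treat any P-value for safety as descriptive and name the version of the test. Fisher's exact test is optional, and its lower power should be acknowledged.

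The cost is a weaker safety claim and a few more table columns. No extra patients or visits are needed, though events must be recorded for patients who stop early.

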## Discussion

Parkinson's disease is a debilitating movement disorder associated with progressive conditions, including sleep disorders, which impair patients' quality of life. While medications are available to manage these issues, patients with Parkinson's disease often are more susceptible to their adverse effects or unable to perform rehabilitative exercises. There is a need for therapies that are not only effective but also accessible to patients with Parkinson's disease.

Because of its successful application in managing myocardial infarction, RIC has been applied to other pathological processes and organ systems to minimize ischemia and reperfusion injury. RIC is an ideal therapy for those with declined mobilities and decreased motivation because it is passively administered.

In addition to the protective effect on ischemic tissue injury, studies have shown that RIC has a neuroprotective (50) and therapeutic effect on sleep (27). Animal studies have found that RIC can rescue approximately half of the functional dopaminergic neurons in the substantia nigra pars compacta damaged by Parkinson's neurotoxin, 1-methyl-4-phenyl-1,2,3,6-tetrahydropyridine (MPTP) (28, 51). RIC has been shown to promote the survival of retinal ganglion cells after various injuries, which plays a large role in the EDS of Parkinson's disease (29–33). Although many studies have proved the safety and effectiveness of RIC in preventing and treating stroke (37), RIC has not been utilized for patients with chronic neurodegenerative diseases. The protective effect of RIC on the brain and retinal optic ganglia suggests that RIC could improve EDS of Parkinson's disease. The duration of RIC in this study is set to be 28 days for safety considerations.

Excessive daytime sleepiness is a common non-motor symptom of Parkinson's disease and manifests as an inability to remain awake during the daytime, fatigue, and sudden collapse. Due to severe dyskinesia in the middle and late stages, patients with Parkinson's disease rely on others for their daily activities. Non-pharmacologic treatment options are currently limited and available therapies, including sports rehabilitation therapy, cognitive behavioral therapy, light treatment, repetitive transcranial magnetic stimulation, and deep brain stimulation (18), are not universally suitable for patients with Parkinson's disease in different stages of their illness. In contrast, RIC is inexpensive and easy to administer especially for patients with risk of falls, limb movement disorder, and inability to participate in traditional rehabilitative activities.

This project will administer RIC to patients with Parkinson's disease in different stages to determine its safety and feasibility. Effectiveness in reducing EDS will be analyzed as well. The results could provide an opportunity to develop a non-pharmacological treatment that is easy and simple to administer for EDS and benefits the community of patients with Parkinson's disease.

